## Abstract

**Introduction:**

The minimally conscious state (MCS) is one of the common and serious complications of stroke patients. Its incidence is higher than that of other types of consciousness disorders. The prolonged monitoring and comprehensive management of patients with MCS imposes substantial socioeconomic burden, creating multifaceted challenges for healthcare systems and considerable strain on familial resources. However, there are still few studies on the treatment of MCS, so there is a lack of standardized and effective treatment for MCS, which needs to be solved urgently. In order to solve this problem, this study proposes a treatment plan of acupuncture for arousal combined with repetitive transcranial magnetic stimulation (rTMS). Acupuncture for arousal is a clinical acupuncture therapy. Accumulating evidence from the published literature indicates that acupuncture for arousal interventions can significantly enhance consciousness levels in comatose patients. Nevertheless, conventional acupuncture monotherapy necessitates extended treatment durations, potentially compromising patient outcomes and neurological recovery trajectories. rTMS can excite or inhibit specific cortical functional areas of the brain, thereby improving the level of consciousness in comatose patients. The significance of this study is to clarify the efficacy and safety of wake-promoting acupuncture combined with repetitive transcranial magnetic stimulation in patients with minimal consciousness after stroke, and to add a standardized and effective scheme for the treatment of MCS. Furthermore, this investigation employs neural-specific biomarkers and functional magnetic resonance imaging to elucidate the mechanisms underlying regional brain functional reorganization. These neuroimaging and molecular approaches may establish a robust scientific foundation for future investigations into consciousness-restoring mechanisms in patients with MCS.

**Methods and analysis:**

This is a single-center design, randomized, controlled, third-party blind trial involving 117 patients. Three groups of patients will receive 4 weeks of treatment. Under basic treatment, the acupuncture for arousal group will only receive acupuncture treatment. The rTMS group only receives rTMS treatment; the combined group is treated with the acupuncture for arousal and rTMS. The main outcome indicators are the GCS score scale, the CRS-R score scale, central nerve-specific protein (S-100B), neuron-specific enolase (NSE), and functional magnetic resonance imaging (fMRI). The secondary outcome indicators are laboratory safety parameters, including routine blood tests, routine urine tests, coagulation tests, electrocardiograms, liver function tests, and renal function tests. Finally, the measurement data and enumeration data will be analyzed via SPSS 25.0 software.

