### Outcome measures

#### Primary outcomes

Our main purpose is to observe the improvement in the level of consciousness in patients with a minimal conscious state after stroke, so we choose some common clinical behavioral assessment scales and brain function test items.

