#### Secondary outcomes

The secondary outcome measures of this study are the safety test items that can assess the patient’s health status and potential safety hazards. It mainly includes routine blood tests, routine urine tests, coagulation tests, electrocardiograms, liver function tests, and renal function tests. These test items can help researchers understand the health status of patients, detect and address possible health problems in time, and ensure the safety of research.

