### Sample size calculation

The GCS score was used as the primary outcome measure for the sample size calculation, following the method outlined by Lai Shilong in the Methodology of Clinical Research of Integrated Chinese and Western Medicine. Based on a study by Li Yuyuan et al. (25), the GCS score for the acupuncture combined with rTMS group was 10.30 ± 3.47 after 4 weeks of treatment. The GCS score for the acupuncture-only group was 8.33 ± 2.97, whereas that for the rTMS group was 8.16 ± 2.98. Taking *α* = 0.05, two-sided test, and *β* = 0.2, the ratio of the three groups of sample sizes was 1:1:1. After the above values are substituted with PASS 15 software, the sample size required for each group is calculated to be 32 cases. Considering a shedding rate of 20%, 39 patients are included in each group, and 117 patients are ultimately included in this study.

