#### Clinical data analysis

SPSS 25.0 software will be used for data analysis. The measurement data will be normally distributed and expressed as mean ± standard deviation (
$\bar{x}$
 ± *s*). Paired *t*-test will be used for comparisons between groups before and after treatment. One-way analysis of variance will be used for the comparison of differences between the three groups, and the *q*-test will be used for comparisons between groups. The *χ*^2^-test will be used for pairwise comparisons of enumeration data, and the Mann–Whitney test and Wallis rank sum test will be used for comparisons among the three groups. *p* < 0.05 will be considered statistically significant.

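### Five outcomes are declared primary with no control of error across them, while the trial is sized on GCS and clinical improvement is judged on CRS-R

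*Protocol article*

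**What the plan says.** The abstract (Methods and analysis) lists five main outcomes: "The main outcome indicators are the GCS score scale, the CRS-R score scale, central nerve-specific protein (S-100B), neuron-specific enolase (NSE"), and, as the fifth, fMRI. The body repeats the list under Primary outcomes, introduced with "so we choose some common clinical behavioral assessment scales and brain function test items", and does not rank one above another. No efficacy or mechanistic measure is placed below them: "The secondary outcome measures of this study are the safety test items".

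Two other sections each single out one scale, and not the same one. Sample size calculation says "The GCS score was used as the primary outcome measure for the sample size calculation", with alpha 0.05 two-sided and beta 0.2. Efficacy evaluation takes CRS-R as its reference standard for the threshold of clinical improvement, the awakening rate and the awakening time.

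Clinical data analysis sets the level for the clinical outcomes (p "< 0.05 will be considered statistically significant") and, after the analysis of variance, says "the *q*-test will be used for comparisons between groups". MRI data analysis states no significance level. Neither section mentions an alpha split, a testing order, or a requirement that all primaries succeed.

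**The concern.** A 5% error rate applies to one deciding test. Here the article declares five primaries, powers one of them, defines clinical success on another, and gives a per-test threshold. The q-test handles the pairs of groups within a single outcome and does nothing across outcomes.

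At stake is what a positive trial would mean. Suppose S-100B falls more in the combined group while GCS does not differ. The article would allow that to be reported as a positive primary outcome, although the error rate assumed in the sample size does not cover such a claim. The Discussion points in that direction: it reads a fall in NSE and S-100B from baseline as a sign that the treatment works, without reference to either scale.

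**Working it through.** **1. The plan's own figure.** Inputs from Sample size calculation: GCS means 10.30, 8.33 and 8.16; SDs 3.47, 2.97 and 2.98; alpha 0.05 two-sided; power 80%; ratio 1:1:1.

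- Grand mean = (10.30 + 8.33 + 8.16)/3 = 8.93. Sum of squared deviations = 1.37² + 0.60² + 0.77² = 2.83.
- One-way analysis of variance, noncentrality = n × 2.83/SD². With a common SD of 2.98 and n = 32 this is 32 × 2.83/8.88 = 10.2, and power is 0.81. The smallest n reaching 80% is 32, which is the stated figure.
- With the root-mean-square SD, √[(3.47² + 2.97² + 2.98²)/3] = 3.15, the smallest n is 35, and power at 32 is 0.76.
- Dropout: 32 × 1.2 = 38.4, rounded up to 39; 3 × 39 = 117, as stated.

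So the stated size can be reproduced as one test, on GCS, at the full 0.05. No part of alpha is reserved for the other four primaries.

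**2. Error across the primaries if any one of them may carry a claim.** For k independent tests at 0.05 the family-wise error is 1 − 0.95^k:

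- k = 5: 1 − 0.95⁵ = 22.6%
- k = 4 (without fMRI): 1 − 0.95⁴ = 18.5%

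The outcomes are likely to be positively correlated, but the article gives no correlations. I therefore assumed an equal pairwise correlation and simulated three groups of 39 with no treatment effect, one F test per outcome at 0.05 (100,000 runs):

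| Assumed correlation | Five outcomes | Four outcomes (no fMRI) |
|---|---|---|
| 0 | 22.6% | 18.6% |
| 0.3 | 21.3% | 17.6% |
| 0.5 | 18.7% | 15.9% |
| 0.7 | 15.2% | 13.2% |
| 0.8 | 13.2% | 11.8% |
| 0.9 | 10.7% | 9.7% |

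Using 32 per group gives the same figures to within 0.2 percentage points.

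This counts one test per outcome. CRS-R alone also supplies a graded response, an awakening rate and an awakening time, and fMRI is a whole-brain regression and not a single F test. More tests could only raise the error.

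**3. What keeping all five as primary would cost.** Bonferroni gives 0.05/5 = 0.01 per outcome, and 1 − 0.99⁵ = 4.9%. With SD 3.15, GCS would need 51 per group instead of 35, or 51/0.8 = 63.75, so 64 per group after 20% dropout. At 32 per group, GCS power falls from 0.76 to 0.53.

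**The case against.** The strongest reply is that the article does separate the roles of its outcomes. Efficacy evaluation judges improvement on CRS-R, so a patient whose biomarkers fall without a change of CRS-R category counts as ineffective there. The abstract and Introduction give the biomarkers and fMRI to the study of mechanism. Testing order and alpha allocation are also often left to an analysis plan, which is not shown.

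Much of this stands. A reader might infer that nothing at all distinguishes the outcomes; the CRS-R section shows otherwise. A reader might also infer that 0.05 governs everything, but it appears under Clinical data analysis and no level is stated for fMRI, which is why the four-outcome figures are given as well. Nor does the article say that one success among the five is enough. No rule excludes it, and the Discussion's sentence on NSE and S-100B leans that way, but that sentence concerns change from baseline and not the between-group test simulated here. Finally, no single inflated rate can be stated as a property of the trial, because it depends on correlations that the article does not supply.

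The reply does not remove the defect. The CRS-R criteria are not a testing hierarchy, and they point to a different scale from the one used for sizing. The point is also not a missing multiplicity section: the article itself fixes five primaries and a per-test threshold, and a later plan could not name one primary without contradicting it.

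**Conclusion.** The point holds as an inconsistency in what the article fixes: five declared primaries, a sample size for GCS alone, clinical improvement defined on CRS-R, and no control across outcomes. On the condition that any one primary may support an efficacy claim, the false-positive risk is about 10-23% for five outcomes or about 10-19% for the four non-imaging ones, for equal correlations from 0.9 down to 0. Even the lowest value is about twice the nominal 5%. If all five had to succeed, the error would not be inflated, but the article does not say so, and power would then have to be shown for all five together.

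The documents do not settle whether GCS or CRS-R should be the single primary. GCS fits the sample size; CRS-R fits the efficacy criteria and the article's own remark that it is especially suited to this population. That choice belongs to the sponsor.

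**What to change.** Before any results are seen, name one primary endpoint at the end of week 4:

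- **GCS**, which agrees with the sample size calculation and leaves 117 patients unchanged; or
- **CRS-R**, which agrees with Efficacy evaluation, with the form of the endpoint stated (total score or response category) and the power restated for it. The article gives no CRS-R means, SDs or response rates, so that needs new inputs.

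Make the other scale a key secondary, tested only if the primary is significant. Class S-100B, NSE and fMRI as mechanistic outcomes that carry no efficacy claim, and bring the Discussion's sentence on NSE and S-100B into line.

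The cost is a protocol and registry amendment and fewer outcomes that can be called primary; no new data are needed. Recruitment was planned from 1 November 2024 to 1 September 2025. If it has begun, the amendment is more than a change of wording: it should be dated, justified and made without sight of outcome data by group.

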**Ethics and dissemination:**

This study has been approved by the Ethics Committee of the Second Chinese Medicine Hospital of Guangdong Province (Approval No.: K202405-003-01, June 19, 2024). The research results will be published in peer-reviewed journals.

**Clinical trial registration:**

https://www.chictr.org.cn/bin/project/edit?pid=235202, ChiCTR2400086163.

## Highlights

This study is the first to combine a traditional therapy (acupuncture for arousal) with a modern neuromodulation technique (repetitive transcranial magnetic stimulation, rTMS), providing a novel multimodal treatment regimen for the patient population (MCS) that currently requires more standardized treatments.In terms of efficacy evaluation, the advantage of this study is to adopt a multi-modal assessment approach, through objective data such as clinical behavioral assessment scales, objective biomarkers (NSE, S100B), and BOLD-fMRI, to comprehensively evaluate the patient 's consciousness recovery level, neurological function recovery and brain function reorganization.Compared with the previous clinical studies of acupuncture, this study innovatively proposed the acupuncture position of sitting position, because acupuncture at neck acupoints can improve the blood supply of vertebral artery and carotid artery, improve the signal of brainstem reticular ascending activation system, and enhance the compensatory mechanism of the brain. In addition, sitting position can induce patients' proprioception.

## Introduction

The World Health Organization defines stroke as “rapidly developed clinical signs of focal (or global) disturbance of cerebral function, lasting more than 24 h or leading to death, with no apparent cause other than of vascular origin” (1). Disorders of consciousness, including coma and other states of impaired consciousness, represent significant, persistent, and clinically challenging complications frequently observed in the post-stroke population. Related studies have shown that approximately 1/3 of stroke patients can experience varying degrees of disturbance of consciousness (2). Modern medical wake-up therapy includes drug therapy, noninvasive brain stimulation [such as repetitive transcranial magnetic stimulation (3), transcranial direct current stimulation (4), percutaneous auricular vagus nerve stimulation (5, 6), etc.], invasive brain stimulation [deep brain stimulation (7) or vagus nerve stimulation (8)], hyperbaric oxygen therapy and traditional Chinese medicine acupuncture therapy. MCS is characterized by severe consciousness impairment following stroke, wherein patients exhibit profound deficits in awareness and cognitive function while demonstrating reproducible, albeit limited, behavioral evidence of self-awareness or environmental perception (9). The incidence of MCS is 10 times higher than that of persistent vegetative state (10). However, there are significantly fewer studies focusing on MCS than on chronic vegetative state and Coma. Despite extensive investigation into diverse neuromodulatory approaches, including various brain stimulation methodologies, targeted anatomical locations, and rehabilitative behavioral interventions, a standardized, evidence-based therapeutic protocol for MCS remains notably absent from clinical practice. Moreover, there is a lack of in-depth discussion on the mechanism of acupuncture improving MCS consciousness. Therefore, the field of awakening in MCS patients is worthy of further exploration in the future (11).

Patients with cerebrovascular accidents who undergo early initiation of comprehensive rehabilitation protocols demonstrate significantly improved survival rates, enhanced functional independence, and more favorable consciousness recovery trajectories compared to those receiving delayed interventions (12). Acupuncture, as part of its comprehensive rehabilitation strategy, is widely accepted in post-stroke disorders of consciousness in China. Acupuncture for arousal (also known as “cuxing acupuncture” in China) is a clinical acupuncture therapy. It is widely used in clinical practice to treat consciousness disorders caused by various cerebrovascular diseases by using specific acupuncture points and manipulations. Previous studies have shown that acupuncture for arousal can improve the level of consciousness in coma and can upregulate the expression of neurotransmitters related to awakening in coma rats after traumatic brain injury (13). The main reason is that the key acupoints of the acupuncture for arousal are located in the neck. Its arousal-promoting mechanism is considered to be related to improvements in the excitability of the brainstem ascending reticular activating system (ARAS) (14, 15). Notably, in addition to the inhibition of ARAS, MCS patients also exhibit a state of cerebral cortex inhibition to a certain extent. Although the early use of the acupuncture for arousal can improve the level of consciousness of MCS patients with stroke, it takes a long course of treatment, and the ratio of patients who can fully wake up successfully is not ideal. Xia et al. (16) reported that 16 patients with disturbance of consciousness (including MCS and unresponsive wakefulness syndrome) improved their consciousness level after receiving high-frequency rTMS in the dorsolateral prefrontal lobe, especially in MCS patients. It has been reported that rTMS-mediated cortical stimulation may activate, inhibit, or interfere with the activity of neural networks (17). For example, high-frequency rTMS increases the excitability of the motor cortex (18). These suggest that high-frequency rTMS is helpful to improve the patient’s state of consciousness.

NSE has neurotrophic and protective properties for neurons. When neurons are damaged or necrotic, cell membrane integrity is destroyed, blood–brain barrier permeability is increased, and NSE levels in serum and cerebrospinal fluid are increased (19). The level of serum NSE in patients with brain injury is significantly higher than that in normal people. The level of serum NSE can reflect the degree of neuronal damage and play an important role in the early diagnosis, evaluation and prognosis of brain diseases (20). S-100B is a specific protein located in the glial cells of the central nervous system. Its level changes can evaluate the degree of nerve cell injury and death, and it is widely used in the prognosis evaluation of patients with stroke and brain injury (21). S-100B can regulate the proliferation, differentiation and energy metabolism of nerve cells, and the damage and apoptosis of nerve cells can promote the release of S-100B. The increase of S-100B level can activate the related nerve signal transduction, regulate the activity of nervous system, and then predict and diagnose brain injury (22).

Compared with other states of disturbance of consciousness after stroke, the incidence of MCS after stroke is high, and patients often need long-term monitoring and treatment to survive, causing great burden and huge economic pressure to society and families (23). In addition, there is no effective and standardized treatment for MCS, so it is of great economic and social significance to find a safe and effective wake-up method for MCS patients. Lam Ching et al. (24) reported that compared with Western medicine, acupuncture alone or plus rTMS, traditional Chinese medicine, traditional Chinese medicine combined with Western medicine were more effective in improving depression symptoms of patients with post-stroke depression. Among all therapeutic strategies evaluated, the combination of acupuncture with rTMS emerged as the most efficacious intervention modality, suggesting potential synergistic neuromodulatory mechanisms warranting further investigation in controlled clinical trials. Therefore, for patients with post-stroke disturbance of consciousness, we put forward the scientific hypothesis that acupuncture combined with rTMS can promote the improvement of consciousness in patients with MCS. This study will utilize acupuncture for arousal combined with rTMS to treat post-stroke MCS, conducting efficacy and safety evaluations to facilitate its future clinical application and to establish a standardized, effective treatment scheme for MCS. Meanwhile, through the detection of neural specific markers and brain functional magnetic resonance imaging, the mechanism of promoting the functional reorganization of brain regions will be discussed, which could provide a more scientific basis for the study of the wake-promoting mechanism of MCS in the future.

**Figure 1 fig1:**
[figure not shown]
The flowchart of this study. rTMS, repetitive transcranial magnetic stimulation; GCS, Glasgow Coma Scale; CRS-R scores, Coma Recovery Scale-Revised; S-100B, central nervous system-specific protein (S-100B); NSE, neuron-specific enolase.

**Figure 2 fig2:**
[figure not shown]
The time points of assessment. rTMS, repetitive transcranial magnetic stimulation; GCS, Glasgow Coma Scale; CRS-R scores, Coma Recovery Scale-Revised; S-100B, central nervous system-specific protein (S-100B); NSE, neuron-specific enolase; fMRI, Functional magnetic resonance imaging.

### Written informed consent

[name], [name], [name], [name], and [name] will obtain the informed consent of the patient’s authorized family members. With written informed consent, all participants will be informed that they will be randomly assigned to any group, with possible benefits and risks. And they will be allowed to withdraw at any time during the study.

### Randomization and blinding

SPSS 25.0 software will be used to generate 117 random numbers between 0 and 1 and rank them. They will be marked and divided into 3 groups (the acupuncture for arousal group, rTMS group, and the acupuncture for arousal combined with rTMS group) and made into cards. These random cards will be placed in opaque, sealed envelopes. The patients will extract the cards according to the order of enrollment and be assigned to the corresponding groups according to the contents of the cards.

Owing to the particularity of acupuncture treatment, this study will not implement a double-blind approach and will only implement a blind evaluation of the efficacy. To reduce detection bias, this study’s efficacy evaluation will be completed by professional evaluators who are not involved in the treatment process and do not know the grouping. These evaluators are senior personnel in the field of coma rehabilitation, with standardized behavioral scale assessment certification qualifications. And before the start of the study, all evaluators will be trained and assessed in a unified manner to ensure the homogeneity of the evaluation criteria.

### Interventions

#### Both groups

Baseline data (including stroke type, family history, and demographic information) will be collected from eligible patients. Before treatment, the GCS score and the CRS-R score will be evaluated, and S-100β, NSE, and fMRI data will be measured. The laboratory test items will be detected for safety evaluation (Table 2).

**Table 2 tab2:** Comparison of baseline characteristics among three groups (before treatment).

Category		Acupuncture for arousal group (*n* = 39)	rTMS group (*n* = 39)	Acupuncture for arousal combined with rTMS group (*n* = 39)	*p*-value
Demographics		-	-	-	-
Age (years, Mean ± SD)		XX ± XX	XX ± XX	XX ± XX	-
Gender (male/female, *n*)		XX (XX%)	XX (XX%)	XX (XX%)	-
Disease duration (days, Mean ± SD)		XX ± XX	XX ± XX	XX ± XX	-
Comorbidities (HTN/DM, etc. *n*)		XX (XX%)	XX (XX%)	XX (XX%)	-
Stroke type		-	-	-	-
Ischemic stroke (*n*)		XX (XX%)	XX (XX%)	XX (XX%)	-
Hemorrhagic stroke (*n*)		XX (XX%)	XX (XX%)	XX (XX%)	-
Severity		-	-	-	-
GCS score (3–15, Mean ± SD)		XX ± XX	XX ± XX	XX ± XX	-
CRS-R Scale	CRS-R total score (0–23, Mean ± SD)	XX ± XX	XX ± XX	XX ± XX	-
	MCS− subgroup (*n*)	XX (XX%)	XX (XX%)	XX (XX%)	-
	MCS+ subgroup (*n*)	XX (XX%)	XX (XX%)	XX (XX%)	-

Age, Disease duration, GCS score, and CRS-R total score are measurement data, and the data will be presented as “Mean ± SD.” Gender, Stroke type, and MCS subgroup are enumeration data, and the data will be presented as “*n* (%).” *p*-value: The *p*-value come from One-way analysis of variance (measurement data) or Mann–Whitney test (enumeration data). If there is no difference between the three groups, then *p* > 0.05. If there is a difference, the specific *p* is marked. HTN, Hypertension; DM, Diabetes Mellitus.

The three groups of patients will undergo basic treatment and corresponding intervention measures for 4 weeks. First, they will be given basic treatment for awakening after stroke, which mainly includes the following:

Drug treatment: For basic diseases (such as hypertension, diabetes and hyperlipidemia, etc.), symptomatic treatment measures are taken, including blood pressure and blood glucose regulation, lipid-lowering and plaque stabilization treatment, anti-platelet aggregation, etc. Concomitantly, the administration of consciousness-altering pharmacological agents with potential neurological modulatory effects should be stringently avoided, encompassing—but not limited to—central nervous system stimulants, cholinergic agonists, and phytotherapeutic/natural compounds possessing arousal-enhancing properties. Furthermore, cerebral metabolic modulators should be systematically excluded from the therapeutic regimen, specifically those that facilitate cerebral bioenergetic processes, enhance neuronal oxygenation or substrate utilization, potentiate neurotransmitter biosynthesis, or exert neuroprotective mechanisms at the cellular or molecular level. There are also prevention and treatment of complications, providing anti-infective drugs to prevent infection, anti-coagulant drugs to prevent thrombosis, drugs to protect the gastric mucosa, and drugs to reduce gastrointestinal complications, etc. And nutritional support treatment, such as providing energy, protein, electrolytes, and vitamin supplements.Specialized nursing: including the placement of functional positions, the correct position can help prevent pressure sores and other problems that may be caused by long-term bed rest. Bladder management and regular emptying of the bladder can prevent urinary tract infections and urinary retention. Artificial airway management, if patients need respiratory support, may need tracheal intubation or other artificial airways. Skin management involves regularly turning over and cleaning the skin and using appropriate mattresses and care products to prevent pressure sores. These will be implemented by a unified professional nursing team.

